### Timeline

[figure not shown]

### Sustainability and Dissemination

Dissemination of research findings requires commitment to both peer reviewed presentation and publication and to strategic efforts with patient and community partners and key stakeholders. Throughout this study, we will distil lessons learned about home and office-based MAT induction to support the provision of MAT in diverse primary care settings. We will utilize formal and informal networks and relationships to disseminate progress and findings.

The research team will identify opportunities for sharing findings throughout the life of the grant to local providers, practices, and communities. We will work closely with the University of Colorado and the American Academy of Family Physicians (AAFP) media departments. We will share findings through regular state and national communication and peer-reviewed publications. We propose regular newsletter articles for the participating practice-based research networks beginning in the first three to six months of the grant. This will provide knowledge of the planned activities and stimulate interest in the project. We will collaborate with local media outlets, including newspapers, television, and radio, to provide updated information on planned efforts, progress, and final outcomes.

#### **D. Description, Risks and Justification of Procedures and Data Collection Tools:**

##### Practice Data

This study will include a process evaluation to describe factors that provide important practice contextual information relevant to data interpretation.

##### *MAT Implementation Checklist*

Upon recruitment, we will administer a MAT Implementation Checklist one person in the practice, such as a Practice Manager, to establish practices' baseline MAT protocols (including any planned adaptations). Where variations exist, we will ensure they do not impact feasibility of data collection and patient safety. If they do not impact these, we will document the variations and determine how they will be included in the outcomes analysis. A study team member will conduct regular monthly check-ins with each practice to establish fidelity to each practice's MAT protocol and document adaptations, review patient recruitment progress, obtain patient drop-out information, and assess utilization of the Practice Participant Tracker (see below). The Checklist will require 8-10 minutes to complete. Practices will have the option to complete the form online or mailed a hard copy (along with a postage-paid envelope to mail completed

Checklists back to the research team at the University of Colorado). The MAT Implementation Checklist is submitted for review and approval (8/24/2020).

### *Key Informant Interviews*

We will conduct semi-structured key informant interviews with approximately 80 individuals from 30-40 participating practices (stratified based on the final sample characteristics and protocol variation) as they complete their follow-up phase (months 18 – 30 of the study). Interviews will be conducted with 2-3 people (combination of clinicians, nurse, and support team members) at each site. The interviews will review MAT protocols and document any adaptations, reasons for the adaptations, unexpected changes and to assess frequency of patient follow-up. These interviews will capture additional contextual information about how the experience differs for home versus office-based inductions. Participants will receive a \$50 gift card.

Interviews will be conducted by research team members by phone and will last approximately 30 minutes. Interviews will be recorded, with respondent's permission. Interviews will be transcribed. No PHI (protected health information) will be collected. No names will be attached to the records. Data will be de-identified. Data from transcripts will be entered into Atlas.ti (qualitative data analysis software) by a project team member for analysis and will be anonymous. Audio files and data from transcripts will be stored on a secure server maintained by the Dept. of Family Medicine (DFM) IT team. Only the study team will have access to the data. Any hard copy notes will be locked in a secure, locked office in DFM. Results will be reported in aggregate format. After analysis is complete, data will be stored according to NIH guidelines. An Information Sheet and Interview Guide will be submitted to COMIRB for approval prior to use.

### *Surveys*

Practice team members will be asked to complete a short Knowledge Survey to measure participants' knowledge of and attitudes towards OUD, MAT, and their practices' OUD management and MAT delivery. They will also be asked to complete a Practice Culture Assessment to help describe practice team's perception of practice characteristics that influence its decision-making processes, leadership, and other aspects of the practice culture. The Practice Knowledge Survey and Practice Culture Assessment are submitted for review and approval (8/24/2020).

Respondents will have the option to complete their surveys online using REDCap or on hard copy. With hard copies, participants will be given a postage-paid envelope to mail completed surveys back to the research team at the University of Colorado.

No names will appear on the surveys. Surveys pose minimal risk to practice members. There is a minimal risk of loss of confidentiality. Survey data from will be confidential and only used by the study team.

### Patient Data

#### *Practice Tracker*

Patient-level data will include the use a Practice Participant Tracker by participating practices to document participant information and clinical care activities. The Tracker will be a binder organized with numbered tabs for each participating patient or electronic Excel file. A spreadsheet for each patient will include a virtual 300-day timeline from initial identification through final data collection. This Tracker will be used to record patient enrollment, completion

of patient MAT education, induction type, induction Day 1 date, prescriptions and refills, urine buprenorphine and urine opioid test results, contacts with patients (when and whether these be via phone, e-mail, or in person), and continuation or discontinuation of treatment. Practices may record information either on paper or electronically with periodic transmission to the central data management team electronically or via secure fax. Summary notes will be recorded from the monthly check-in calls with practices. A template copy of the Practice Participant Tracker will be submitted to COMIRB for review and approval prior to use. Practices will receive \$200 for each patient enrolled from their practice (up to 12) and \$35 per patient per month for up to nine months of monitoring maintaining follow-up with each patient in their Practice Participant Trackers, paid at the end of the data collection phase.

### Surveys

Patient participants will be asked to complete questionnaires and assessments (surveys) pertaining to social determine of health and quality of life. Surveys will be administered at baseline, 30 days, 90 days, and 270 days. Participants will receive a \$50 gift card (e.g., Amazon, Walmart) per time (baseline, 30 days, 90 days, and 279 days), totaling up to \$200 in gift cards. Respondents will have the option the complete their surveys online using REDCap or on hard copy. With hard copies, packets will include a postage-paid envelope to mail completed surveys back to the research team at the University of Colorado. Final selection of these questionnaires and assessment will be made and submitted to COMIRB for review and approval prior to use.

A summary of the study measures and potential data collection tools is shown in Table 1.

Table 1 Outcomes, Measures, and Potential Data Collection Tools

| Outcome                                                                                                                                                   | Measure                                                                                                                                                                                                                                                                        | Data Collection Tool(s)                                                                                                                                                                                                                                                                                                                                                                   |
|-----------------------------------------------------------------------------------------------------------------------------------------------------------|--------------------------------------------------------------------------------------------------------------------------------------------------------------------------------------------------------------------------------------------------------------------------------|-------------------------------------------------------------------------------------------------------------------------------------------------------------------------------------------------------------------------------------------------------------------------------------------------------------------------------------------------------------------------------------------|
| Primary Outcomes                                                                                                                                   | Timing of data collection indicated by *, **, †, ‡, §, ¶                                                                                                                                                                                                                |                                                                                                                                                                                                                                                                                                                                                                                           |
| Number of days patient took buprenorphine between Day 1 and Day 270†                                                                                      | 
 
▪ Prescription refills†
 
▪ Patient self-report of number of days buprenorphine taken†
 
                                                                                                                                | 
 
▪ Practice Participant Tracker
 
                                                                                                                                                                                                                                                                                                          |
| Number of days patient took illicit opioids between day 1 and day 270**‡                                                                                  | 
 
▪ Patient self-report of number of days other opioids taken†
 
▪ Patient urine opioid test results‡
 
                                                                                                                   | 
 
▪ Practice Participant Tracker
 
                                                                                                                                                                                                                                                                                                          |
| Took buprenorphine on ≥80% of days between 1 and 270                                                                                      | 
 
▪ Initial prescription and refills†
 
▪ Patient self-report of number of days buprenorphine taken†
 
▪ Patient urine buprenorphine test results‡ (Above data converted to yes/no measure)

 
 | 
 
▪ Practice Participant Tracker
 
                                                                                                                                                                                                                                                                                                          |
| Percent (%) of patients that took other opioids on <10% of days between 1 and 270                                                                         | 
 
▪ Patient self-report of number of days other opioids taken†
 
▪ Patient urine opioid test results‡
 
                                                                                                                   | 
 
▪ Practice Participant Tracker
 
                                                                                                                                                                                                                                                                                                          |
| Patient-Centered Outcomes±                                                                                                                         |                                                                                                                                                                                                                                                                                |                                                                                                                                                                                                                                                                                                                                                                                           |
| Social Determinants of Health and Quality of Life                                                                                                         | Patient surveys completed per clinical care on quality of life (e.g., symptoms, side effects, depression), social connectedness, loneliness, and other select determinants of health**                                                                                         | 
 
▪ NIH PROMIS or SF 12 or 20
 
▪ Activity and Participation Questionnaire
 
▪ Social & Community Opportunities Profile
 
▪ UCLA 3-item Loneliness Scale
 
▪ American Academy of Family Physicians Social Determinants of Health tool
 
 |
| Patient-Level Moderators and Mediators±                                                                                                            |                                                                                                                                                                                                                                                                                |                                                                                                                                                                                                                                                                                                                                                                                           |
| Moderators 
 
▪ Substance Use History
 
▪ Substance Use Appeal
 
▪ Executive Function
 
 | Patient Surveys completed per clinical care on quality of life*                                                                                                                                                                                                                | 
 
▪ PROMIS short form measures – Appeal and Severity of Substance Use
 
▪ Behavior Rating Inventory of Executive Function–Adult, self-report version)
 
                                                                                                                                                    |

|                                                                                                                                                                                                                                                                                                                                                                                                                                                   |                                                                                                                                                                                                                                                                                                                                             |                                                                                                                                                                                                                          |
|---------------------------------------------------------------------------------------------------------------------------------------------------------------------------------------------------------------------------------------------------------------------------------------------------------------------------------------------------------------------------------------------------------------------------------------------------|---------------------------------------------------------------------------------------------------------------------------------------------------------------------------------------------------------------------------------------------------------------------------------------------------------------------------------------------|--------------------------------------------------------------------------------------------------------------------------------------------------------------------------------------------------------------------------|
| Mediators 
 
▪ Motivation
 
▪ Planning
 
▪ Automaticity
 
                                                                                                                                                                                                                                                                                                                       | Patient Surveys completed per clinical care on quality of life**                                                                                                                                                                                                                                                                            | 
 
▪ Health care climate questionnaire
 
▪ Intention measure
 
▪ Planning measure
 
▪ Self-Report Habit Index
 
 |
| Demographics                                                                                                                                                                                                                                                                                                                                                                                                                               | Patient Surveys*                                                                                                                                                                                                                                                                                                                            | 
 
▪ Patient Demographic Survey
 
                                                                                                                                           |
| Practice-Level Moderators                                                                                                                                                                                                                                                                                                                                                                                                                  |                                                                                                                                                                                                                                                                                                                                             |                                                                                                                                                                                                                          |
| Contextual Factors                                                                                                                                                                                                                                                                                                                                                                                                                                | 
 
▪ Aspects of practice culture, leadership, decision-making collected from all members of participating practices*
 
▪ Practice type, number of providers, number of waived providers, practice MAT training, duration of MAT provision completed by knowledgeable practice member*
 
 | 
 
▪ Practice Culture Assessment
 
▪ Practice Characteristics Survey
 
                                                                                               |
| Process Measures                                                                                                                                                                                                                                                                                                                                                                                                                                  | 
 
▪ Medication assisted treatment protocols, completed by knowledgeable practice member*
 
▪ Fidelity & adaptations to MAT protocols♦
 
                                                                                                                                            | 
 
▪ IT MATTRs MAT Implementation Checklist
 
                                                                                                                  |
| 
*Collected at baseline only (patient data collected during consent process)
 
**Collected at baseline, 30 days, 90 days, and 270 days after induction
 
‡ Collected at 30, 90, and 270 days after induction
 
¥ Collected at ≥2 office visits
 
♦Collected during Monthly Check-In Calls
 
± To be discussed with the Project Community Advisory Council to determine final selection of instruments and measures
 |                                                                                                                                                                                                                                                                                                                                             |                                                                                                                                                                                                                          |

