### Randomization

Patients who meet eligibility criteria and consent to participate will be randomized to either the *office-based induction* arm or the *home induction* arm. Both induction methods are evidence-based approaches for initiating MAT in patients with OUD. Participating practices will receive a suggested protocol for both office-based and home inductions. However, practices and providers experienced in MAT may have their own existing protocols for office and home induction. Given the pragmatic nature of this trial, we will allow some variation in induction protocols.

Randomization will occur at the patient level. Patients will be informed that participation includes randomization by the initial information handout they receive from the practice and again by the research team member during the consent process. Randomization will occur immediately following consent. A study coordinator will inform the participant of their randomization assignment. As consent will be completed by phone with the patient, the study team member will inform the participant of the study arm assignment (randomization result) while on the phone with the participant and then immediately inform the practice of the patient's assigned induction type.

A block randomization process will be used where patient participant "slots" will be randomized for each practice in advance of recruitment to ensure equal distribution between arms at each practice. This will increase our power to detect differences between study arms, as opposed to a cluster randomized trial. Further, this use of block randomization will provide the best opportunity for each practice to enroll patients in either arm of the study and for regular monitoring of enrollment across arms. Few previous studies on home and office-based MAT induction have been randomized trials. The study findings will be the result of rigorous research design and methods.

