### *Patients*

Interested potential participants (with a diagnosis of OUD and seeking to begin MAT) will receive a study informational packet at their clinic, which will include a copy of the [Postcard Consent Form](#). The practice will call the research team member assigned to them with the patient's contact information for patients that have expressed interest in the study and given the practice permission to initiate contact with the research team. If the patient is interested and willing to learn more at that visit, referred here to as Time 1, the practice will call the research team member assigned to them with the patient's contact information for patients that have expressed interest in the study and given the practice permission to initiate contact with the research team. A member of the research team will describe the study in detail to the patient, confirm eligibility, consent and randomize the patient, and contact the practice with the study arm. If this step cannot occur at Time 1, the practice will transmit to the central study team the interested and eligible patients' contact information for later informed consent and randomization. The goal will be to contact eligible, interested patients within 4 days of Time 1. At what is referred to here as Time 2, the patient will undergo MAT induction, per protocol for the method (home or office-based). We will strive to complete consent and randomization such that practices schedule Time 2 (induction) with 5 – 15 days of Time 1.

A signed, hard copy of the [Postcard Consent Form](#) will not be required from participants. The research team member will obtain and document verbal consent in REDCap. The [Postcard Consent Form](#) will explain that participation is voluntary and that they can discontinue participation at any time, the nature of participation, and that all data are confidential. For children age 16 and 17, we will obtain parent or guardian contact information to contact the parent. Parents or guardians will be informed of the study purposes and procedures. We will contact the child to obtain assent only after consent is obtained from the parent or guardian.

Although patients will be consented, each survey will still include a brief Information Sheet reviewing the conditions of participation, including that participation is voluntary and confidentiality. In addition to documentation of verbal consent by the study team, completion of surveys and assessments will imply consent.

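### The baseline quality-of-life and social scores can be completed after the patient has been told the arm, and H3 uses them as its first outcome point

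*Protocol*

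**What the plan says.** **Order of events (Protocol, IV.C, Randomization).** "Randomization will occur immediately following consent". Consent is taken by phone, and "the study team member will inform the participant of the study arm assignment (randomization result) while on the phone with the participant". No step for a baseline survey is named between consent and randomisation.

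**Surveys relative to consent (Consent, Patients).** Surveys go to people who have already agreed to take part: "Although patients will be consented, each survey will still include a brief Information Sheet reviewing the conditions of participation".

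**How surveys are completed (IV.D, Patient Data, Surveys).** "Surveys will be administered at baseline, 30 days, 90 days, and 270 days". Patients may choose between REDCap and paper on all four occasions, and nothing sets baseline apart. For those who choose paper, the plan is that "packets will include a postage-paid envelope to mail completed surveys back to the research team".

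**Table 1 notes.** The single asterisk marks the patient moderators, the demographics and several practice-level items. Its note is "Collected at baseline only (patient data collected during consent process". The double asterisk marks quality of life, the social measures and the mediators. Its note is "Collected at baseline, 30 days, 90 days, and 270 days after induction", with no reference to the consent process.

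**Use of the baseline score (Data Analysis Plan, H3).** Baseline, 30, 90 and 270 day scores all enter a random coefficient growth curve model, and H3 is tested by the time-by-arm interaction. Quality of life and social functioning are the fifth item in the list of primary outcomes (IV.A).

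**The concern.** H3 asks whether one arm improves more than the other. Patients know whether they are assigned to home or office induction, and the scores are their own reports. If the first score is given after the patient has heard the arm, it may already contain a reaction to the assignment. A shift confined to that first score looks like a difference in improvement. It can create an apparent effect or hide a real one.

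Adjusting for a baseline that the arm has already moved does not remove the bias. Comparing follow-up scores alone would avoid it, but that is not the planned H3 analysis and it gives up the baseline information. The order of data collection is set by the protocol. A statistical analysis plan cannot restore a clean baseline once the data are in.

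**Working it through.** **1. Can the baseline survey precede disclosure as the text stands?**

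- Consent, randomisation and disclosure follow one another on a single call (Randomization).
- A paper survey posted back cannot be completed and returned inside that sequence. If handled as written, it comes after disclosure.
- An online survey could be completed before disclosure, but no passage requires it.
- The Table 1 note that mentions the consent process is not attached to the quality-of-life, social or mediator rows. Even if it applied to them, randomisation and disclosure share the consent call, so collection during the consent process is not the same as collection before disclosure.

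**2. The plan's own power figure.** The protocol states 81% power for continuous outcomes with 400 to 500 per arm and a difference of 0.20 to 0.18 SD, two-sided alpha 0.05. The formula is power = Φ(δ/√(2/n) − 1.96).

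- n = 400, δ = 0.20: 0.20/0.0707 − 1.96 = 0.87, giving 80.7%.
- n = 500, δ = 0.18: 0.18/0.0632 − 1.96 = 0.89, giving 81.2%.

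The stated figure reproduces.

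**3. Effect of a baseline shift on the H3 slope.** Let d be the arm difference, in SD units, that knowledge of the assignment puts into the mean baseline score and into no later score.

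- Visits on a scale where 270 days = 1: 0, 0.111, 0.333, 1. The mean is 0.361.
- Sum of squared deviations: 1.1235 − 4 × 0.361² = 0.602.
- Weight of the day-0 score in the slope: (0 − 0.361)/0.602 = −0.60.
- Size of the slope bias over 270 days: 0.60 × d, opposite in sign to the shift.

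| d (assumed) | Slope bias |
|---|---|
| 0.05 SD | 0.03 SD |
| 0.10 SD | 0.06 SD |

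For scale, 0.06/0.20 is 30% of the difference used in the power statement.

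**4. False-positive rate with no true effect.** Inputs are 400 per arm (the protocol's figure after attrition), complete data, unit variance and an assumed within-patient correlation of 0.5.

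- SE of the slope difference: √(2 × 0.5/(0.602 × 400)) = 0.0645.
- Rejection probability: 1 − Φ(1.96 − bias/SE) + Φ(−1.96 − bias/SE).
- d = 0.05: bias/SE = 0.47, giving 7.5%.
- d = 0.10: bias/SE = 0.93, giving 15.4%.

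Three other sets of assumed variance components were tried (intercept, slope, residual): 0.5, 0.3, 0.3 with intercept–slope covariance 0; the same with covariance −0.1; and 0.6, 0.2, 0.4. The weight stays at −0.60, and the rates run from 7.4% to 7.6% and from 14.9% to 15.8%.

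**5. What d means.** It is an average over everyone in the comparison. If half the patients completed the baseline after disclosure, d = 0.05 would need an arm difference of 0.10 SD among them (0.5 × 0.10), and d = 0.10 would need 0.20 SD (0.5 × 0.20).

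**The case against.** - **The Table 1 note may cover all patient baseline data.** The single asterisk also marks practice-level items, so its mention of patient data may only separate patient from practice baseline. The moderator and mediator rows describe their surveys in the same words, and there is one baseline occasion with one gift card. This stands. A reader might infer from the asterisks that the quality-of-life baseline is deliberately collected at a later occasion; the table does not show that. The note still does not say before disclosure, and it conflicts with postal return.
- **Patients with a preference are excluded.** Eligibility (IV.B) and Participant Recruitment limit the trial to people willing to use either method. This weakens the reaction to assignment. It does not remove it, because a patient without a prior preference can still respond to the news.
- **The envelope sentence is general.** It covers all four occasions and does not say that any baseline survey will be posted. True, but it makes no exception for baseline.
- **Completion after induction.** Because induction is aimed at 5 to 15 days after the first visit, a reader might infer that baselines will include early treatment effects. The text sets no latest date, so this is possible, but nothing says it will happen.
- **Larger error rates.** For a day-270 minus baseline score with correlation 0.5, the same shifts give 10.9% and 29.3%. The protocol plans a growth curve, not that score, so these figures should not be held against it.

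**Conclusion.** The concern holds as a gap in the order of collection. As written, the protocol allows the baseline quality-of-life, social functioning and mediator scores to be completed after the patient knows the arm. A paper baseline returned by post cannot come before disclosure on the same call. The quality-of-life and social scores are the first outcome point of the H3 test.

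The documents do not show that a shift will occur, how large it would be or in which direction. The rise in the false-positive rate from 5% to about 8% to 15% is an illustration. It rests on an assumed baseline-only shift of 0.05 to 0.10 SD, a correlation of 0.5, 400 complete patients per arm and no true effect. A reaction that persisted equally at every visit would not bias the slope.

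H1 and H2 have no baseline value and are unaffected; H3a is touched only through H3. The change is worth making because it is cheap now and the baseline cannot be recovered later.

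**What to change.** State in the protocol that all baseline patient instruments (quality of life, social functioning and social determinants, mediators, moderators) are completed and time-stamped after consent and before randomisation or disclosure of the arm. This can be done by phone or REDCap link in the same contact, or before a short call-back at which the arm is given. Completion of the baseline survey can be made a REDCap condition for releasing the assignment. Limit paper and postal return to the 30, 90 and 270 day surveys. Then reconcile the Randomization section, the Surveys section and the Table 1 notes, so that the consent-process note plainly covers, or plainly does not cover, the double-asterisk items.

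The sample size does not change. The cost is protocol wording, a REDCap setting and a longer first contact. Some patients will be randomised later or not at all, which matters for a trial that aims to enrol 1200. Losses before randomisation reduce recruitment but do not bias the comparison between arms.
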